#### Eye-tracking battery

The eye-tracking tasks will be recorded with the EyeLink1000 Plus system (SR Research, Ontario, Canada), monocularly (left eye) at 1000 Hz. All tasks will be preceded by a calibration sequence. Tasks will be analysed with SR Research’s analysis program ‘DataViewer’ and with custom-made programs in MATLAB.

##### Fixation task

A fixation cross will be presented in the centre of the screen and participants will be required to fixate on it for the entire duration of the task (1 min). This task will be analysed in terms of the rate of ‘saccade intrusions’, namely square wave jerks (pairs of saccades moving the eye away and back to central fixation within 200 ms).

##### Prosaccade task

Target dots will appear at different angles to the left and right (at 5°, 10° and 15°), with pseudorandomised timing and location. Participants will be required to look at the dots when they appear. The task will involve 78 trials and will be analysed for latency (saccadic reaction time to the target stimulus), gain (saccadic amplitude divided by target amplitude giving a measure of saccadic ‘accuracy’) and peak velocity (peak speed of saccades).

##### Antisaccade task

Dots will appear at different angles (5°, 10° and 15°), with pseudorandomised timing and location. Participants will be required to not look at the target when it appears on screen, but to immediately look the same distance from the centre of the monitor but in the opposite direction of where the stimulus appeared. The task will consist of 78 trials and will be analysed in terms of the rate of errors, and the gain, latency and peak velocity of correct responses. A practice task will be conducted first to ensure participants understand the instructions.

##### Memory-guided task

Participants will be asked to fixate on a cross in the centre of the screen while another stimulus is presented briefly in the periphery (50 ms; 5°, 10° or 15° horizontally). The stimulus will disappear after a short period and then the participant will be required to look at (make a saccade towards) where they recall the stimulus in the periphery to have appeared. The task will involve 52 trials and will be analysed in terms of inhibitory error rate (a saccade made to the briefly presented stimulus before being cued to do so), directional error rate (once cued to make a saccade, making a saccade in the opposite direction of the presented stimulus), as well as gain, latency and peak velocity of correct responses and inhibitory errors. Participants will complete a practice task.

##### Facial affect task

Participants will be asked to examine a target black and white photograph showing one of six human models (three females and three male), each displaying one of seven universal emotions. The photographs will be presented for 5 s, with 64 trials. After the photograph is removed, participants are required to identify the shown emotion using a forced-choice paradigm by clicking the mouse “happy”, “sad”, “anger”, “surprise”, “disgust”, “fear” or “neutral”. This task will include a photograph of the participants’ own face (if they consent), displaying a neutral emotion. Participants will initially complete a practice task to ensure they understand the instructions.

##### Body attractiveness task

Participants will be asked to rate the attractiveness of human body stimuli (25 females and 25 males in black clothing). Stimuli will be presented for 5 s, with 50 trials. After each human body is shown, participants are required to click with the mouse on a scale of 1 (least attractive) to 7 (most attractive).

##### Visual search task

Participants will be shown a collection of shapes (red and blue triangles facing different directions) and are required to search for a particular target among the distractor shapes. Specifically, participants are required to search for a red triangle pointing towards the right (target), which may or may not be present in each visual scene. A screen then asks if the target shape was present, and participants can respond by clicking with the mouse on ‘yes’ or ‘no’. Seventy trials of increasing difficulty will be presented, with each presented for 5 s. A practice trial will be conducted first, to ensure participants understand the task.

#### Brief assessment to track change

The assessment to track for any change throughout the three phases of visual training will include a brief symptom severity measure of BDD and a short eye-tracking task. The memory-guided saccade task was chosen as pilot work has indicated that it might be a useful indicator within this population, with inhibitory error rate as the variable of interest. This brief assessment will take approximately 15 min to complete and is composed of the Dysmorphic Concern Questionnaire (DCQ) and Memory-guided eye-tracking task, as described above.

At the beginning of each week’s visual training activities, participants will also complete a brief self-report questionnaire (please see Additional file 2) to assess how much time and effort, if any, they have spent practicing or thinking about the previous weeks training. This will attempt to control for any homework practiced by participants alongside the required visual training program activities.

### Planned interventions

The visual training program will involve three phases of visual training presented in a bottom-up order of processing, based on the literature of visual abnormalities present in BDD. This program will be administered by provisional psychologist FB and involves a grand total of 16.8 h of training (90 min per week), based on the recommendations of general cognitive remediation research [46, 47, 50, 53, 56]. The following tasks from Posit Science will be presented using the ‘Personalised Trainer’ format, where the administrator predetermines certain exercises, but presentation is based on individual performance. The administrator can observe participation and progress to monitor adherence. Participants are free to withdraw from the intervention at any time on their request.

#### Phase 1: Basic visual training

The first phase of the visual training program involves training in basic and general visual principles (such as scanning, attention, movement and details), using the Posit Science (Brain HQ) computer-training module. This phase will be administered in one-on-one face-to-face sessions with provisional psychologist FB who will instruct and support the participants. Specific visual training tasks were selected on the basis of relevant basic visual processes.

Visual sweeps improves overall visual acuity and speeds up visual processing. Participants are required to watch two patterns that ‘sweep’ in or out and identify the direction of the movement by clicking with a mouse. As participants improve, the exercise can change in terms of the speed, colours, direction and thickness of the sweep patterns. Baseline speed presents each sweep for 200 ms and adjusts according to the participant’s accuracy (e.g. speeds up presentation if previous answer was correct). Visual sweeps includes four different stages of colour and direction, with each task consisting of 30 trials. Total score is the presentation time (in milliseconds of the final trial).

Target tracker improves divided attention. Participants are required to keep track of target objects among distractor objects and click on the targets with the mouse when all of the objects stop moving. The exercise increases in difficulty as objects travel faster, the contrast decreases between the objects and background and the exercise adapts to participants’ performance by changing the number of target objects. Target tracker includes four different stages of speed and contract, with each task consisting of 10 trials. Baseline begins with two target objects to track, with additional target objects added or removed according to the participant’s accuracy (e.g. more targets added if previous answer was correct). The total score is the overall number of items tracked accurately.

Eye for detail improves ability to make saccades quickly and to notice subtle details, using visual working memory. Three to five images appear, one at a time, in different positions on the screen. Of the pictures, some match precisely, while others are similar, but not identical. Participants are required to identify where the two identical images appear by clicking on the positions with the mouse. As participants improve, the images flash by more quickly, become more similar and therefore harder to distinguish, are spread further apart so the eyes must move a farther distance and graduate from three to five images. Eye for detail includes four different stages of speed and discrimination, with each task consisting of 18 trials. Baseline speed begins by presenting each image for 500 ms and adjusts according to the participant’s accuracy (e.g. speeds up presentation if previous answer was correct). Total score is the presentation time in milliseconds of the final trial.

Hawk eye improves visual precision and working memory. Participants are required to identify the one image of a bird that is different from the other birds presented within their peripheral vision by clicking on the position with the mouse. The birds initially appear very distinct, close together and on a simple background, but as participants progress through the exercises the birds become more similar, are spread farther apart and the background becomes more complex. Hawk eye includes two different stages of speed and discrimination, with each task consisting of 35 trials. Baseline speed begins by presenting each image for 200 ms and adjusts according to the participant’s accuracy (e.g. speeds up presentation if previous answer was correct).Total score is the presentation time in milliseconds of the final trial.

#### Phase 2: Face specific visual training

The second phase of training involves visual training specifically relating to faces, including facial recognition and emotion recognition. All tasks will be administered through the Posit Science (Brain HQ) computer-training module. This phase will be administered in one-on-one face-to-face sessions with a provisional psychologist, who will instruct and support the participants. Specific visual training tasks were selected due to the relevance of visual face processing within BDD.

Face to face improves social cognition and visual processing speed, so participants can quickly and correctly interpret facial expressions. Participants are briefly shown a face and are then required to decide what expression they think it shows. They then choose the face showing the same expression from a set of faces by clicking with the mouse. As participants improve, more emotions are added, the intensity of the expression decreases, the faces flash up faster and the number of faces to choose from increases. The initial facial expressions include happy, sad, neutral, angry and surprised and then expand to include afraid, disgusted, proud, contemptuous, puzzled and embarrassed. Face to face includes six different stages of number of emotions, and intensity of emotional expression, with each task consisting of 20 trials. Baseline speed begins by presenting each image for 1000 ms and adjusts according to the participant’s accuracy (e.g. speeds up presentation if previous answer was correct). Total score is the presentation time in milliseconds of the final trial.

Recognition improves facial recognition and visual processing speed, so participants can quickly and accurately identify an individual’s face from a group of other faces. Participants are briefly shown a face and then required to identify which one they saw from a selection of faces, by clicking with the mouse. As participants improve, the angle of the face changes (straight on, 45° angle and profile), the number of faces to choose from increases, the faces flash up faster, and the faces become gender-matched. Recognition includes six different stages of number of faces, and characteristics of faces, with each task consisting of 20 trials. Baseline speed begins by presenting each image for 500 ms and adjusts according to the participant’s accuracy (e.g. speeds up presentation if previous answer was correct). The total score is the presentation time in milliseconds of the final trial.

#### Phase 3: Self-perception visual training

The third phase involves perceptual retraining using mirrors. This phase will be administered in one-on-one face-to-face sessions with a provisional psychologist, in accordance with the ‘Perceptual Retraining for Mirror Checking’ chapter from ‘Cognitive Behaviour Therapy for Body Dysmorphic Disorder: A Treatment Manual’ [83].

Mirror retraining helps to change how individuals look at themselves in the mirror, to a more mindful, nonjudgmental and holistic way, resulting in improved self-perception. This involves systematic exposure to mirror reflections while asking clients to take a different perspective than they typically do, e.g. see self holistically instead of focusing or avoiding hotspots. The purpose is to help clients gradually feel less anxious each time they look in a mirror, by changing the focus of their perception. Each exercise should take around 10 min. The provisional psychologist administering the visual training program has received specialised training in CBT for BDD, including perceptual mirror retraining.

### Sample size

As this is a pilot study, sample size calculations were not considered appropriate. The authors aimed for 20 participants as it was deemed that this sample size would be sufficient in assessing the practicalities of recruitment, intervention delivery and attrition in a clinical population. This sample size is sufficient in exploring qualitative themes of acceptability and reflects quantitative measures of clinical outcomes within this population.

### Analysis

The feasibility outcomes of recruitment rate, retention rate, adverse events, compliance and acceptability will be reported using a descriptive approach with 95% confidence intervals for any estimates. The qualitative data regarding acceptability will be subjected to, thematic analysis following Braun and Clarke’s (2006) guidelines. To prevent potential coding bias, the researcher conducting the semi-structured interview will not participate in the coding. The final coding structure will be validated with the remaining members of the research team.

Clinical outcomes will be reported as means, standard deviations and ranges for all outcome measures at T1–T4, with between-group differences analysed using a repeated measures analysis of variance (MANOVA). Due to the underpowered nature of the pilot trial, these results will focus on point estimates and associated 95% confidence intervals as opposed to significance testing, to explore potential efficacy of the program. Missing data will be dealt with by adopting appropriate imputation procedures which will include mean or last observation carried forward.

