**Methods:**

This is a single-group open-label pilot study assessing the feasibility and potential efficacy of a 10-week visual training program. This pilot trial will be conducted at Swinburne University of Technology, Melbourne, Australia, and will recruit up to 20 participants diagnosed with BDD. These participants will complete pre- and post-assessments and a 10-week visual training program encompassing three phases of basic visual processing, face and emotion recognition, and self-perception. The primary outcomes focus on feasibility and acceptability of the intervention, with secondary outcomes exploring clinical outcomes related to symptom severity, quality of life and eye movements.

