## Methods

### Design

Due to the innovative nature of this visual training program, this research will employ a single-group pre-post pilot study design. All recruited participants will take part in the visual training program, with baseline assessments conducted at T1 and T4 after the 10-week program has been completed. All participants will be invited to complete the outcome assessment regardless if they complete the 10-week program or not. Participants will also be asked to complete change assessments at T2 (4 weeks) and T3 (8 weeks) to assess for any specific changes on outcome measures after each phase of the trial is complete. Please see Fig. 1 for the Consolidated Standards of Reporting Trials (CONSORT) flow diagram of the study procedure. The present trial was designed in consideration of the CONSORT extension to pilot studies [59]. Table 1 summarises activities and timing of participation, which will result in a total of 16.8 h training over 10 weeks. Participants will be reimbursed with $50 when they complete each of the pre- and post-assessments and will be given $70 to cover costs for travel over the total 10-week training and assessment period.

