## Discussion

Despite the growing literature of visual processing abnormalities being a core feature of BDD, this is rarely a target of treatment [58]. Indeed, only one study to date has attempted to alter visual perception among this population, with limited but promising findings [39]. Due to the poor long-term treatment outcomes and high relapse rates reported among BDD, there has been overwhelming support for a visual training program to address the often-neglected area of visual perception. As such, this pilot study aims to evaluate the feasibility and potential efficacy of a visual training program to remediate visual abnormalities and reduce symptom severity of individuals with BDD. It is expected that this program will show promising feasibility and acceptability outcomes, which may lead to the implementation of a definitive RCT which would be appropriately powered to assess efficacy compared to a control group. Additionally, clinical outcomes may demonstrate potential efficacy in terms of symptom severity, quality of life and eye movement data.

One practical issue of this study may involve recruitment numbers, based on the nature of BDD. As the disorder is such a secretive one, population estimates can be low, and those that have been diagnosed or identify with having BDD are often housebound or otherwise significantly impaired in daily functioning. As such, there may be some difficulty arranging for participants to attend a 10-week visual training program outside of their home. The authors propose that by framing this trial as a novel intervention study with the opportunity to learn new skills, individuals may see the potential benefits of participating.

Generalisability is another possible issue for this trial, as due to the often varied nature of BDD, the sample will only capture a small percentage of this population. In addition, individuals interested in participating in a treatment trial are likely to have certain traits which may distinguish them from the broader clinical population, such as increased motivation, and higher likelihood of concurrent psychological or psychiatric treatment. The authors acknowledge the bias implicit in a single-group open label pilot study, due to the lack of control group and randomisation. However, this methodology is believed necessary to initially explore the feasibility of such a program prior to a definitive RCT.

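### The clinical analysis names a between-group contrast that a one-group trial does not have, and promises four-timepoint summaries for outcomes that are mostly measured only twice

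*Protocol article*

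**What the plan says.** The Design section states that "this research will employ a single-group pre-post pilot study design". The abstract agrees ("This is a single-group open-label pilot study assessing the feasibility and potential efficacy of a 10-week visual training program"), and the Discussion acknowledges bias "due to the lack of control group and randomisation".

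The Analysis section says "Clinical outcomes will be reported as means, standard deviations and ranges for all outcome measures at T1–T4", and the same sentence continues "with between-group differences analysed using a repeated measures analysis of variance (MANOVA". The next sentence says that "these results will focus on point estimates and associated 95% confidence intervals as opposed to significance testing".

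Under Design, T1 is baseline, T2 is week 4, T3 is week 8, and T4 follows the 10-week program. T2 and T3 are change assessments, and the section on the brief assessment says that this assessment "is composed of the Dysmorphic Concern Questionnaire (DCQ) and Memory-guided eye-tracking task". The Clinical outcomes section places the clinical interview, the self-report questionnaires and the eye-tracking tasks in the pre- and post-assessments.

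The Aims and Table 1 also show a brief change assessment at week 10. Table 1 then lists a separate final assessment after it.

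**The concern.** Two statements in one sentence conflict with the rest of the protocol. The contrast needs a second group, and there is none. The reporting schedule needs T2 and T3 values of all outcome measures, and most of them have none by design.

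The model label adds to the difficulty. A repeated-measures analysis of variance and a MANOVA are not the same analysis, and the text treats one as the abbreviation of the other.

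This matters because it is the only model named for the clinical outcomes. The secondary objectives ask for estimates, variances and signs of efficacy, and for data to size a definitive RCT. If the stated contrast must be replaced, the replacement should be written before the data are analysed. Otherwise the analyst has a free choice among many clinical measures.

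**Working it through.** The plan gives no figure to reproduce; the Sample size section says that no calculation was made. The check is therefore of what can be estimated.

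**Inputs.** Number of groups G = 1 (Design). Target n = 20 (Sample size). Minimum enrolment counted as success n = 10 (Feasibility and acceptability). Visit content comes from Clinical outcomes, Brief assessment to track change, and Table 1.

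**1. The between-group contrast.** Degrees of freedom = G − 1 = 1 − 1 = 0. Equivalently, in a model with an intercept and a group term, the group column is constant, so the design matrix has rank 1 of 2. More participants do not change this.

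**2. The reporting schedule.**

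| Measure | Pre (T1) | Week 4 (T2) | Week 8 (T3) | Week 10 change assessment | Final assessment |
|---|---|---|---|---|---|
| DCQ, memory-guided task | yes | yes | yes | yes | yes |
| BDD-YBOCS, AQoL-4D, other questionnaires, other eye-tracking tasks | yes | no | no | no | yes |

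For the second row, T2 and T3 means, SDs and ranges do not exist. For the first row there appear to be five scheduled measurements and four labels, so T4 could be the week-10 or the final assessment.

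**3. What one group does support.** With k timepoints, the time effect has k − 1 and (k − 1)(n − 1) degrees of freedom in the univariate form, and k − 1 and n − k + 1 in the multivariate form.

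| | n = 20 | n = 10 |
|---|---|---|
| k = 4, univariate | 3 and 57 | 3 and 27 |
| k = 4, multivariate | 3 and 17 | 3 and 7 |
| k = 2 | 1 and 19 | 1 and 9 |

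At k = 2 the F statistic is the square of the paired t.

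**4. The estimates the plan promises.** The 95% CI for a mean T1-to-T4 change has half-width t(0.975, n − 1)/√n, in units of the SD of change:

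- n = 20: 2.093/4.472 = 0.47
- n = 10: 2.262/3.162 = 0.72

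These intervals need the SD of change. It does not follow from the SDs at each visit, because SD(change)² = SD(T1)² + SD(T4)² − 2r·SD(T1)·SD(T4), where r is the correlation between the two visits. Summaries by timepoint alone therefore do not supply it.

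**The case against.** The best defence is that this is a slip of wording. The design is plainly pre-post, so change over time is the evident intent. The same paragraph already commits to point estimates and confidence intervals, and the T1–T4 phrase can be read as each measure at the times when it is collected. The SD of change is detail that an analysis plan not shown here may supply. The clinical outcomes are secondary and exploratory in a pilot that its authors call underpowered.

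Much of this stands, and it limits the point. It does not remove it: the text as written names a contrast that does not exist and a schedule that the visit content contradicts, and a reader must replace both to reach the intended analysis.

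A reader might infer three stronger claims, which the document does not support:

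- *That the clinical analysis cannot be run or cannot give the promised estimates.* A repeated-measures model on time is estimable in one group, and paired changes with confidence intervals are available for every outcome measured at T1 and T4. Only the between-group contrast and the T2/T3 summaries of twice-measured outcomes are impossible.
- *That a MANOVA fails because there are more outcomes than participants.* The text lists at least 12 scales and 16 fixation and saccade parameters, 28 in all, and a joint analysis of change becomes singular above n − 1 = 19 outcomes at n = 20. But the protocol does not say that outcomes enter jointly. The label can equally mean the multivariate form of a repeated-measures analysis of one outcome, which works (3 and 17 degrees of freedom at n = 20).
- *That anyone with a missing visit is dropped.* The Analysis section plans imputation, and Design invites all participants to the outcome assessment whether or not they finish the program. Whether the named imputation methods are good ones is a separate question.

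**Conclusion.** The point holds as an error in the stated analysis, of moderate severity. The between-group contrast has 0 degrees of freedom and is not estimable. The four-timepoint summary is possible only for the DCQ and the memory-guided task. The model label is ambiguous rather than unworkable.

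The consequence is confined to the secondary clinical estimates, including those meant to inform the definitive RCT. The primary feasibility and acceptability outcomes are analysed descriptively with 95% confidence intervals and are not touched.

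The conclusion on the contrast rests only on there being one group, which the protocol states in several places. The conclusion on the schedule rests on the visit content as the article gives it. The interval widths assume complete pairs at n = 20 or n = 10.

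**What to change.** Amend the Analysis section as follows:

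1. Replace the between-group contrast with within-participant change from T1.
2. For every clinical outcome, report the mean T1-to-T4 change with its 95% CI and the SD of change. Keep the means, SDs and ranges, given at the times when that outcome is measured.
3. Limit the four-timepoint summaries and the time model to the DCQ and the memory-guided task.
4. Name one model in place of the double label, for example a per-outcome repeated-measures model with time as a categorical factor.
5. State whether T4 for the DCQ and the memory-guided task is the week-10 change assessment or the final assessment, and what is done with the other measurement. Make the Aims, Design and Table 1 agree.

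The cost is a few sentences, with no new data, visits or participants. The change should be made and dated before the clinical data are analysed.

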### Outcomes

#### Feasibility and acceptability

The primary outcomes of this trial focus on feasibility and acceptability, with secondary outcomes evaluating clinical measures. Feasibility will be assessed in terms of recruitment numbers (success defined as minimum of 10 participants enrolled over a period of 12 months), completion (with completers defined as participants who complete 100% of the proposed intervention) and attrition rates (success defined as less than 20% attrition), adverse events and fidelity to the protocol as defined by protocol violations.

Acceptability of the intervention will be assessed using a specifically designed qualitative interview, to explore participants’ experiences and feedback. A semi-structured interview will be administered which was developed by the research team, including those with experimental and clinical experience working with body dysmorphic disorder (please see Additional file 1). Thirteen questions will be asked, encompassing the following:

Overall experience, for example, tell me what you thought about the program?General benefits, for example, what did the program do for you?Stimulus, for example, what tasks did you like the most?Cognitive trainer, for example, what did you think was the role of the provisional psychologist?Structure of session, for example, did you like the way the sessions were run?

This interview will be audio recorded with the participant’s consent. Participants will be given the opportunity to provide any additional feedback not queried in the interview, and the interviewer may clarify any aspects as necessary. Participants will also complete the Helping Alliance Questionnaire (HAQ) to assess the presence of therapeutic factors which may have contributed to the results. The HAQ is a well-validated measure for assessing patients’ perceptions of the quality of the therapeutic alliance [60, 61].The authors established guidelines for specific feasibility and acceptability criteria in determining whether a future definitive RCT may be undertaken. These criteria included (a) the proportion of participants referred/contacted participating in the visual training program would be 50% or greater, (b) the proportion of participants completing the visual training program would be 50% or greater and (c) the qualitative feedback would predominantly reflect participant satisfaction with the visual training program with less than 30% reporting negative perceptions.

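### Filling missing clinical outcomes by the mean or by last observation carried forward gives 95% confidence intervals that are too narrow, with method-specific damage to the SDs (mean) or to the estimated change (LOCF)

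*Protocol article*

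**What the plan says.** The Analysis section states: "Missing data will be dealt with by adopting appropriate imputation procedures which will include mean or last observation carried forward". It gives no rule for which method applies to which outcome or visit, and names no likelihood-based method, multiple imputation or sensitivity analysis, although the wording leaves the list open.

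The same section makes intervals the main clinical output: "these results will focus on point estimates and associated 95% confidence intervals as opposed to significance testing". It also says "Clinical outcomes will be reported as means, standard deviations and ranges for all outcome measures at T1–T4". The secondary objectives (Study goals and objectives) include assessing estimates and variances of the clinical outcomes and gathering data to size a definitive RCT.

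On numbers, "The authors aimed for 20 participants", and "sample size calculations were not considered appropriate". The section on the brief assessment to track change shows that only the DCQ and the memory-guided saccade task are repeated during the program. The other clinical measures, such as the BDD-YBOCS, the AQoL-4D and the remaining eye-tracking tasks, are taken before and after only.

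**The concern.** A single filled-in value carries no uncertainty, yet the analysis treats it as a measurement. The sample is counted as 20 when fewer people were observed. Point estimates, intervals and variances are the quantities this pilot is meant to deliver on clinical outcomes, so the missing-data rule acts on them directly.

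The two methods do different harm. Group-mean filling adds people with no spread, which lowers the SD of the filled variable. LOCF on a measure with no interim value carries the baseline to T4, which enters a change of exactly zero. At stake are the honesty of the intervals, the size of the reported change, and the SD that a later RCT might inherit.

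**Working it through.** The plan gives no SD, effect size or power, so there is no figure of its own to reproduce. Changes are in units of the true SD of change, except where the four-visit simulation is named.

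**Inputs.** n = 20 (Sample size). Missing at T4: 2, 4 or 10. Four of 20 is the 20% attrition limit (Feasibility and acceptability); 10 of 20 borrows the 50% completion limit as an extreme. Two is an illustration of light loss. Effect sizes are assumptions, shown over a range.

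**Group-mean imputation of change scores, m observed of n.**
- SD factor = √((m−1)/(n−1)).
- Half-width after imputation = t(0.975, n−1) × SD factor / √n.
- Half-width from observed cases = t(0.975, m−1) / √m.
- Under missing completely at random (MCAR), coverage = P(|T| ≤ width ratio × t(0.975, m−1)), with T on m−1 degrees of freedom.

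| Missing | m | SD factor | Half-width, imputed | Half-width, observed | Ratio | Coverage |
|---|---|---|---|---|---|---|
| 2 | 18 | √(17/19) = 0.95 | 0.443 | 0.497 | 0.89 | 92% |
| 4 | 16 | √(15/19) = 0.89 | 0.416 | 0.533 | 0.78 | 88% |
| 10 | 10 | √(9/19) = 0.69 | 0.322 | 0.715 | 0.45 | 66% |

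**Effect on a later RCT, if it used that SD.** Assume a difference of 0.5 true SD, two-sided 5% and 80% power. Per arm, n = 2 × (1.960 + 0.842)² × s² / 0.5² = 62.8 s², where s is the SD factor. The true SD gives 63. With 4 missing, 62.8 × 15/19 gives 50; with 10 missing, 62.8 × 9/19 gives 30. True power, Φ(0.5√(n/2) − 1.960), is then 71% and 49%.

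**If the T4 score is filled with the T4 group mean instead.** This was simulated with 10,000 trials of n = 20, four visits, visit SD 1, a true change of −0.80 and a baseline-to-post correlation of about 0.46.
- MCAR, 20% and 50% missing: the T4 SD falls to 0.87 and 0.66 (observed cases 0.98 and 0.97). The change SD is almost unchanged (1.01 and 1.00), the mean change is unbiased (−0.80), and coverage is 92% and 84%.
- Dropout more likely with a worse T2 score: the mean change becomes −0.91 and −1.05, with coverage 90% and 75%.
- Observed cases in the same data: about 95% coverage under MCAR. With T2-dependent dropout, −0.77 and −0.73, with coverage 95% and 94%.

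**LOCF, baseline carried, missing fraction d, true change δ, SD of change s.**
- Mean change = (1−d)δ: a loss of 20% with 4 missing, 50% with 10.
- Variance of change = (1−d)s² + d(1−d)δ². This is below s² only if |δ| < s/√(1−d), that is 1.12 SD at d = 0.2 and 1.41 SD at d = 0.5.
- At δ = 0.8 SD, the interval width relative to observed cases is 0.83 (4 missing) and 0.53 (10 missing).
- The T4 SD rises, by factors of 1.05 and 1.08 in the same example.

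Simulated coverage with 4 missing at random is about 94%, 92%, 89% and 87% for true changes of 0.25, 0.5, 0.8 and 1 SD. With 10 missing it runs from 86% to 32% between 0.25 and 1 SD. The shortfall grows with the true change because the interval is both narrow and centred on a shrunken value.

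**LOCF where interim values exist** (four-visit simulation, MCAR): −0.70 and −0.56 against −0.80, with coverage 93% and 78%.

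**The case against.** Several points on the other side stand.

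- A reader might infer that both methods bias the change and shrink the SDs. They do not. Group-mean filling leaves the mean change unbiased under MCAR, and LOCF can raise the SD.
- A reader might infer that the RCT is bound to be under-sized. The document does not say that imputed SDs will be used for planning. If T4 scores are filled, the change SD hardly moves. A target effect shrunk by LOCF would push the sample size up.
- A reader might take "the proportion of participants completing the visual training program would be 50% or greater" as a forecast of 50% missing outcomes. It is not: completers must finish the whole intervention, while the Design section says "All participants will be invited to complete the outcome assessment regardless if they complete the 10-week program or not" and each pre- and post-assessment is reimbursed. Four missing also already fails the attrition target, "attrition rates (success defined as less than 20% attrition". With 2 missing the damage is modest: coverage about 92% for the mean, and no lower than about 93.5% for LOCF at changes up to 1 SD.
- The word mean may refer to filling skipped items from a person's other items. The SD formula would then not apply.
- A condensed article may leave the choice per outcome to a fuller plan, so the missing allocation rule carries little weight by itself.
- Clinical outcomes are secondary, and none of the three RCT progression criteria uses a clinical estimate, SD or interval.

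These points limit the consequences. They do not remove the defect: the article itself names two single imputations as the approach, beside a stated reliance on intervals and variances. Inviting non-completers back reduces missing data but cannot guarantee attendance.

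**Conclusion.** The concern holds in a limited form. Over the range examined, both methods give intervals narrower than the observed data support. Group-mean filling multiplies interval width by 0.89 with 2 missing and 0.78 with 4 (0.45 at the extreme of 10) and shrinks the SD of whichever variable is filled. It biases the mean change only when dropout is related to outcome. LOCF reduces any improvement by the missing fraction on measures taken only before and after, and does not consistently shrink SDs.

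The mean-imputation figures assume group-mean filling of change scores under MCAR. The LOCF coverage figures depend heavily on the assumed effect, for which the document offers no value. The under-sizing of an RCT is conditional on a shrunken SD being carried into its calculation. The primary feasibility conclusions and the progression criteria are unaffected.

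**What to change.** Remove mean imputation and LOCF of whole outcome scores as the main approach, and state instead:

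- For the DCQ and the memory-guided inhibitory error rate, fit a likelihood-based mixed model with time as a categorical factor to all observed data, without imputation. It uses the interim scores of people who leave and is valid if missingness depends only on observed values.
- For measures taken only before and after, report the observed n and the mean paired change with its 95% CI, or fit the same model to T1 and T4.
- Take SDs intended for RCT planning from observed values only.
- Keep LOCF, if wanted, as a labelled sensitivity analysis.
- If the mean was meant for skipped questionnaire items, say so and give the rule.

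This changes analysis wording only. The cost is wider intervals: with 4 missing, a half-width of 0.533 SD where group-mean filling would show 0.416 SD. The wider one reflects the number of people actually observed.
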